# 2. COVID-19 CLINICAL PROFILE

Important published research studies on COVID-19 were selected to tabulate the data on symptoms (Table 1), timelines of the course of disease (Table 2), complications (Table 3) and co-morbidity (Table 4).

COVID-19 is an acute respiratory tract infection. Though the clinical phenotype is similar to influenza, the spread and severity of illness is much more in case of COVID-19. The overall mortality of COVID-19, albeit due to respiratory complications, seems to be several folds higher than that of influenza. And unlike influenza, there is no vaccine or specific drugs to kill the virus.

Viral RNA levels have been demonstrated from upper respiratory and lung specimens. In over 90% cases, the viral RNA tests on nasopharyngeal swabs was found to be repeatedly negative at about 10 days after the onset of symptoms but the viral shedding may continue well beyond clinical recovery; median duration 20 days (range of 8 to 37 days) (9,10). In mild infections, the virus may not be detected especially if the viral RNA level in respiratory specimen is less than 106 copies/mL. Some recent studies have also shown prolonged virus shedding in stool samples.

The incubation time of COVID-19 is about 5-7 days and the infectivity is often high much before the onset of symptomatic illness (11). The infection remains asymptomatic in a substantial proportion of community and a predominant proportion of symptomatic cases will suffer from mild to moderate cases. However, asymptomatic individuals may show abnormalities in the lungs on computed tomography (CT) scans (12). It is estimated that less than 20 % cases will rapidly progress to severe stage and develop life threatening lung and systemic complications requiring critical care and often life support systems like ventilators. The overall mortality rate is about 2-3%. According to the WHO, the recovery time appears to be around two weeks for mild infections and three to six weeks for severe disease.

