**11.2 Secondary Efficacy:**

1) Rate of patients with negative SARS-CoV-2 on nasal or throat swab in a 2-day continuous real time RT-PCR test beginning from ‘first day of clinical recovery’ (see above) or ‘Day 10 after onset of symptoms depending on whichever of the two time points is first achieved

2) Timelines (days counted from onset of illness) - normal body temperature <37◦C, absence or minimal cough (see ‘clinical recovery’ for the definition), absence of dyspnoea (respiration rate 24/minute or less on room air), onset of clinical pneumonia, pneumonia diagnosed on chest X-Ray or CT scan, time to supplemental oxygen, admit in intensive care unit, mechanical ventilation (non-invasive), mechanical ventilation (invasive), steroid use, respiratory failure, adult respiratory distress syndrome, cytokine storm syndrome, secondary infection, shock, septicaemia shock, hospital discharge, death, negative nose or throat swab confirmatory test, all-cause mortality (Time Frame: up to 28 days).

Note: In case of symptoms, the absence on improvement should be sustained for at least 72 hours or live hospital discharge, whichever comes first.

3) Proportion OF patients developing an event that reflects clinical or otherwise improvement of worsening (the events are similar to those listed under Timelines, see above)

4) Improvement on pulmonary function tests using simple ‘home expiratory spirometer’ device and peripheral pulse oximetry

5) Improvement in selected laboratory parameters: blood haemoglobin, differential and total leukocyte counts, liver enzymes, renal functions, acute phase reactants, serum IL-6 and other selected cytokines, serum muscle enzymes (CK, CPK), serum ferritin, serum d-Dimer, anti-oxidant markers, serum BNP (cardiac function)

6) Serological Protective Antibody Assay (IgM and IgG)

7) Radiological Improvement on digital chest Xray and HRCT chest

8) Drug related: side effects and toxicity, and tolerability

9) Health status: WHO QOL (Appendix M) brief, health related behaviour habit and fitness questionnaire based on visual analogue scale (See Appendix N)

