**17.2 Statistical Analysis:**

Whenever suitable, both completer and an intent-to-treat analysis with ‘last observation carried forward’ will be performed; for intent-to-treat analysis the patient should have completed at least 4 weeks of intervention and completed the follow up visit at 4 weeks post enrollment.

All statistical processing will be performed using SPSS & BMDP software unless otherwise stated.

The data will be individually analyzed for central tendencies (mean, median), range, standard error, standard deviation and 95% confidence intervals for each intervention arm in each of the groups in the study. Data will be tabulated and graphically shown using standard format and MS Excel and other software programs. Though ANOVA will be used for most of the measures, standard parametric (Student t-test) and non-parametric statistical tests (Mann Whitney statistic, Kruskal Wallis test) will be used depending upon the normality of the data. Fisher’s exact test or Chi Square will be used to test the proportion of patients classified as efficacy failures and those with AE (calculate exact binomial 95% Confidence Interval).

The primary efficacy measures of ‘mean time to clinical recovery’ and ‘proportion of patients with clinical recovery’ in the two arms will be compared using appropriate statistical tests; ANOVA for ‘mean time’ and two proportion z-test for proportion of patients.

Secondary efficacy measures in the two arms will also be compared and Bonferroni correction will be applied for multiple comparisons.

Risk ascertainment will be done for selected variables. Regression analysis (multivariate and step down) will be used to identify predictors for important outcomes. Survival analysis will be carried out to compare the two interventions (HCQ and Ashwagandha) for primary efficacy at different study time points.

Within arm efficacy will be evaluated by a one sample Student t-test.

Significance for each statistical test result will be considered at two-sided p< 0.05.

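### The worsening timelines have no rule for patients without the event, so the named tests would compare arms only among patients who worsened, which can hide a benefit or make it look like harm

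*Combined protocol and SAP*

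**What the plan says.** Section 11.2, item 2 defines the outcome as "Timelines (days counted from onset of illness"). The list includes "time to supplemental oxygen, admit in intensive care unit, mechanical ventilation (non-invasive), mechanical ventilation (invasive), steroid use", continues through respiratory failure, ARDS, cytokine storm and shock, and ends with "all-cause mortality (Time Frame: up to 28 days"). It gives no number of days, censoring rule or competing-event rule for a patient in whom the event does not occur.

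Item 3 of the same section makes a separate outcome of the proportion of patients "developing an event that reflects clinical or otherwise improvement of worsening (the events are similar to those listed under Timelines, see above").

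Section 17.2 sets the default: "Though ANOVA will be used for most of the measures, standard parametric (Student t-test) and non-parametric statistical tests", chosen according to normality. On secondary outcomes it says only: "Secondary efficacy measures in the two arms will also be compared and Bonferroni correction will be applied for multiple comparisons". Survival analysis appears once, for primary efficacy.

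Section 2 gives a general figure for COVID-19: "It is estimated that less than 20 % cases will rapidly progress to severe stage".

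**The concern.** A patient who never enters intensive care has no number of days to intensive care. ANOVA, the t-test and the rank tests cannot use a patient without a number, and the plan assigns none. Applied as named, they leave only patients who had the event. Having the event is itself something the drug may change, so the two groups being compared are no longer the randomised groups.

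At stake is the meaning of the result. Mean days to a bad event among those who had it does not measure how many patients were spared. If the drug spares patients who would have worsened late, those left in its arm are the early ones, and the drug appears to bring the event forward. Items 2 and 3 could then point in opposite directions for the same event, and the plan does not say which governs.

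**Working it through.** **Plan's own figure.** There is no power, effect size or event count to reproduce for the timelines. Section 17.1 gives a convenience sample of 70 per arm (2 × 70 = 140).

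**How many patients have a value.** Expected events per arm = 70 × event rate. The rates are assumptions; 20% is the ceiling of the general figure in Section 2.
- 5%: 3.5 events, 95% of patients without a value
- 10%: 7 events, 90% without
- 20%: 14 events, 80% without

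Section 2 supports rates of this order for severe-stage events. It does not do so for oxygen or steroid use. Table 6 shows nasal oxygen in 21 to 77% and steroids in 19 to 45% of the hospital cohorts reviewed, and Section 3 keeps patients on non-invasive oxygen within mild to moderate disease. The trial's own rates for these two are unknown.

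**Hand example.** Control: 14 of 70 have the event, 7 on day 8 and 7 on day 14. Mean = (7 × 8 + 7 × 14)/14 = 11.0 days. The drug prevents the 7 late events, leaving 7 of 70 on day 8, mean 8.0 days. Risk is halved (20% to 10%), yet the drug looks 3 days worse. The item 3 comparison of 14/70 with 7/70 points the right way (Fisher p = 0.15).

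**Main illustration.** Assumptions: 70 per arm, 20% control event rate, event day gamma-distributed with mean 10.5 and SD 4, all events after Day 10.5 prevented.
- Shape = (10.5/4)² = 6.89; scale = 4²/10.5 = 1.52.
- P(event day ≤ 10.5) = 0.55, so about 14 × 0.55 = 7.7 events remain on drug.
- Mean day among those is 7.6, so the difference is 10.5 − 7.6 = 2.9 days, shorter on drug.
- Simulated share of trials with a significant t-test in the wrong direction: about 38% at 0.05; about 8% at 0.05/9 = 0.0056 (nine secondary items in Section 11.2); about 4% at 0.05/20 = 0.0025 (20 timelines in item 2). The plan does not state the size of the Bonferroni family, so this is a range.
- At a 10% control rate the unadjusted figure is about 15 to 16%. At 5% it is about 6% of all trials, and the comparison can be computed in only about half of them.

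**Equal prevention.** Same assumptions, but the drug halves events regardless of timing (14 versus 7). Mean days do not differ and the t-test rejects 5% of the time. Fisher's test on the proportion rejects 31% of the time at 0.05.

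**Dependence on which events are prevented.** A second timing model puts half the control events near day 8 and half near day 14 (SD 2.5), with a 20% control rate and events halved overall. Share of computable trials in which the drug arm looks faster to the event:
- all late events prevented: 97%
- 80% of late and 20% of early: 84%
- early and late equally: 49%
- 20% of late and 80% of early: 15%

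In the first of these, a log-rank test on all 140 patients, with event-free patients censored at Day 28, was significant in the right direction in 36% of trials and in the wrong direction in about 0%.

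**The case against.** **The plan does not say that only worsened patients are compared.** True. A reader might take the restriction as a stated rule, but it follows from the methods named and the absence of any scoring rule. Section 17.2 applies ANOVA to most measures, not all, and the synopsis objectives also give the timelines a descriptive purpose. But Section 17.2 still says the secondary measures are compared between arms, and every test it names for continuous measures needs a number per patient. If another rule is intended, it has to be written down before the data are seen.

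**Item 3 already compares the same events as proportions.** This stands, and it limits the damage: a misleading timeline would sit beside a proportion without the conditioning problem. The documents therefore do not support the stronger inference that the trial as a whole would miss or reverse a benefit. Item 3 does not replace item 2, however, and both are to be tested.

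**More than 80% event-free for every listed event.** The Section 2 figure invites that reading. It concerns progression to severe disease among cases generally, and the plan does not show it for oxygen or steroid use. The conditioning problem applies to those two as well, but its extent is unknown.

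**The 38% is an extreme case.** It combines the ceiling event rate, prevention of late events only and no multiplicity adjustment. Section 17.2 prescribes Bonferroni, which brings it to about 4 to 8%, and would lower the power of the proportion test as well. Bonferroni does not remove the 2.9-day bias in the estimate.

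The trial is also labelled exploratory and these are secondary outcomes, which bears on the weight of the point but not on its validity.

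**Conclusion.** The gap is real. Under the methods named in Section 17.2, event-free patients drop out of the worsening timelines, and the remaining comparison is conditioned on a post-randomisation event. For severe-stage events that would exclude most patients. The direction of the error depends on the drug: equal prevention of early and late events makes the benefit invisible in days, mainly late prevention makes it look like harm, and mainly early prevention gives the right sign. A reader might infer that the analysis will reverse the drug's effect; the plan supports only that it can.

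The size rests on assumed rates and timing. In the main illustration the bias is about 2.9 days, with wrong-direction significance of about 38% unadjusted and about 4 to 8% under the plan's own correction. This warrants a change of method for a secondary outcome; it does not affect the primary outcomes.

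**What to change.** In Sections 11.2 and 17.2:
- Do not test mean days for the worsening events in item 2.
- For each non-fatal worsening event, name one between-arm comparison: the item 3 proportion by Day 28, or the cumulative incidence from randomisation to Day 28 with death as a competing event (for example Gray's test). Counting from randomisation starts the comparison where the arms were formed and matches the primary outcome in Section 11.1.
- Make it in all randomised patients, including those withdrawn on progression (Sections 9 and 10) and without the requirement in Section 17.2 of 4 weeks of intervention and the week 4 visit. Otherwise patients with events may be lost from this analysis too.
- Analyse death and all-cause mortality by Kaplan-Meier and log-rank or as a Day-28 proportion, since death cannot compete with itself.
- Report days from onset among affected patients descriptively only.

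The cost is wording. No new data item is needed, although follow-up of withdrawn patients, which Sections 9 and 10 already foresee, has to be carried out. The change corrects the direction of the comparison, not its power: 20% versus 10% has about 38% power at 70 per arm at 0.05, and 80% power would need 199 per arm.

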**Table 2: COVID-19 TIMELINES OF THE COURSE OF DISEASE (LITERATURE REVIEW#):**

| **Study** | **Wang et al.^1^** | **Li et al.^2^** | **Huang et al.^3^** | **Zhou et al.^4^** |
| --- | --- | --- | --- | --- |
| **Site** | China | China | China | China |
| **Study type** | Retrospective  Observational  Single center | Prospective  Observational  Multicenter | Prospective  Observational  Single center | Retrospective  Observational  Multi center |
| **Nature of Site** | Hospital | Hospital | Hospital | Hospital |
| **Sample size** | 138 | 425 | 41 | 191 |
| **Time to symptoms- Median days (IQR)** | | | | |
| **Fever** | -- | -- | -- | 1 (1-1) |
| **Cough** | -- | -- | -- | 1 (1-3) |
| **Dyspnoea** | 5 (1-10) | -- | 8 (5-13) | 7 (4-9) |
| **1^st^ Hospital visit** |  | 4.6 (95%CI 4.1-5.1) | 8 (5-13) | -- |
| **Hospital admission** | 7 (4-8) | 9.1 (95%CI 8.6-9.7) | 7 (4-8) | -- |
| **Time to complications- Median days (IQR)** | | | | |
| **ICU admission** | -- | -- | 10.5 (8-17) | 12 (8-15) |
| **Mechanical Ventilation** | -- | -- | 10.5 (7-14) | 14.5 (12-19) |
| **ARDS** | 8 (6-12) | -- | 9 (8-14) | 12 (8-15) |
| **Sepsis/ Shock** | -- | -- | -- | 9 (7-13) |
| **Acute Cardiac injury** | -- | -- | -- | 15 (10-17) |
| **Acute Kidney injury** | -- | -- | -- | 15 (13-19.5) |
| **Time to outcome- Median days (IQR)** | | | | |
| **Discharge** | -- | -- | -- | 22 (18-25) |
| **Death** | -- | -- | -- | 18.5 (15-22) |
| **Recovery** | 10 (7-14) | -- | -- | -- |
| **Others** | -- | -- | -- | Viral shedding:  20 (17-24)  Severe disease:  19 (17-22)  Critical disease:  24 (22-30) |

ARDS: Acute respiratory distress syndrome. IQR: Interquartile range, CI: Confidence interval.

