**Fig 1: Study Flow diagram showing Study Events and Timelines**

Screening of Voluntary and Consenting In-patients suffering from Mild to Moderately Severe COVID-19 for Eligibility as per Inclusion-Exclusion Criteria

3 Ayurveda formulation drug trial studies under a common protocol

(Separate study for each AYUSH 64 / Yashtimadhu / Samshamai Vati Plus)

Randomize Eligible Hospitalized Patients

(Open Label, Parallel Efficacy, Active Control Standard of Care (SOC), Two Arm Study)

Selected Ayurveda Formulation (Adjuvant) Versus SOC (Active Control)

Time Points

Clinical Assessment

Investigations

Baseline

Case Record Form (CRF), Medical History Clinical Examination, Ayurveda Assessment, Health Status (WHOQs), QoL (HR-BHF)

Diagnostic (PCR), Serology (IgM, IgG), Routine Hematology Profile, Special Assays, X-Ray Chest & Imaging, ECG

Week 4

Brief Clin Exam, Ayu Exam, Health Status (WHO- Qs) & QoL (HR-BHF Qs), Adverse Events (AEs)

Diagnostic (PCR), Serology (IgM, IgG), Routine haematology Body Profile, Special Assays

Week 8

Brief Clin Exam, Ayu Exam, Health Status (WHO- Qs) & QoL (HR-BHF Qs), Adverse Events (AEs)

Diagnostic (PCR), Serology (IgM, IgG), Routine haematology Body Profile, Special Assays

Week 12

Completion Outcome Assessment, CRF Clin Exam, Ayu Exam, WHO- Qs & QoL (HR-BHF Qs), AEs

Diagnostic (PCR), Serology (IgM, IgG), Routine haematology Body Profile, Special Assays

***Further Assessment Time Points**: (i) During Hospitalization: Daily monitored vital parameters, disease symptoms, disease progression and recovery, and investigations carried out as per protocol till DISCHARGE; Laboratory and Imaging investigations as per protocol but the study investigator and treating physician can do any additional test as per their judgment (ii)Post DISCHARGE: Daily Telephonic Contact using a special mobile phone application for any relapse or any other symptoms or complications or any other Issue (iii) Discharge: Complete all formalities as required for study completion (iv) Skip week 4 or week 8 end point evaluation within 2 weeks of DISCHARGE

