# CONSENT, SELECTION, SCREENING, and ENROLLMENT

Study patients will be served on first come first serve basis as per the protocol.

Consenting and eligible patients will be enrolled as soon as possible in a COCID-19 management facility and the study intervention begun. It is important that symptomatic patients suspected for COVID-19 on clinical grounds are quickly evaluated for eligibility. It is important to enroll the patient as close to the onset of symptoms as possible. As described above, this study is dealing with patients of COVID who are ‘non-emergent’ which means mild and moderate disease (pneumonia) which does not require emergency or critical care (see section on inclusion and exclusion criteria).

An ‘Patient Information Sheet’ (Appendix F) in the language understood by the patient will be provided to each patient for study and discussion prior to enrollment. The information fact sheet will describe the overall design of the study and the rationale, benefit and side effect profile of the study drug interventions, and other aspects of the study.

Patients will be selected from the outpatient or inpatient facility in COVID-19 medical centres/ hospitals. The study will be explained to the volunteer patients and those willing to sign the informed consent (Appendix G) will be screened for eligibility as per the inclusion and exclusion criteria in the protocol.

Though it will be preferable to enrol patients with diagnosis confirmed by a positive RT-PCR assay using a nasal or throat swab in a standardized procedure, a patient with a clinical diagnosis of COVID- 19 as described below will be eligible.

Eligible patients will be enrolled using a simple randomization table (provided to the investigator) in a block of 20 patients each to either of the two study arms - SOC plus Ayurveda drug or SOC. As the target sample size is 70 patients in each arm, the first block of randomized allocation will be of 10. The study randomization will be carried out by the investigator.

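### After a positive first swab pair no repeat PCR is specified until Week 4 (or discharge from about Day 14), so for late-enrolled, early-discharged patients clearance between about onset Day 11 and Day 28 goes unobserved, with no censoring rule

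*Combined protocol and SAP*

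**What the plan says.** Section 11.2, item 2 defines a set of secondary outcomes as "Timelines (days counted from onset of illness" and closes the list with "negative nose or throat swab confirmatory test, all-cause mortality (Time Frame: up to 28 days". The synopsis version of the item has no 28-day limit.

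The swabs come from two places.

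- **Swabs tied to the illness.** Item 1 of Section 11.2 has a two-day RT-PCR pair that starts on the first day of clinical recovery or "Day 10 after onset of symptoms depending on whichever of the two time points is first achieved".
- **Swabs tied to the calendar.** Fig 1 (Section 5) lists PCR at baseline, and "Diagnostic (PCR), Serology (IgM, IgG), Routine haematology Body Profile, Special Assays" at Weeks 4, 8 and 12. The Schedule of Events (Appendix A, Table 1) has no PCR row.

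Week 4 runs from enrolment: Section 17.2 admits a patient to the intent-to-treat analysis only if he or she has "completed the follow up visit at 4 weeks post enrollment".

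Three provisions can move or add a swab. Appendix A, note ii, merges the Week 4 investigations with those at discharge when discharge falls within two weeks of Week 4; the clinical evaluation section has a similar rule for slow recoverers, while Fig 1 says to skip that evaluation. Section 19.10 lets a visit move 3 to 5 days either way. Appendix A, note i, lets the treating physician order any test at any time.

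For analysis, Section 17.2 names ANOVA for most measures, with t-tests and rank tests according to normality, and carries the last observation forward. Survival analysis is named only for primary efficacy, and there it names two drugs that are not the products under study.

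**The concern.** A time to negative swab is only as good as the swabs that bracket it. Here the illness-linked pair comes early and once, and the next required swab is tied to a different clock. A patient still positive at the pair, enrolled some days after onset and sent home in the usual time, may turn negative well within 28 days of onset without any required test showing it.

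This has two consequences. First, the recorded time is largely the day of the pair. Where recovery comes before illness Day 10, recovery sets that day. An arm that recovers sooner is then swabbed sooner and can show an earlier negative swab with no difference in clearance. Second, patients positive at the pair have no clearance day in the window, and the plan does not say how they enter the comparison.

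**Working it through.** The plan gives no figure to reproduce for this outcome, so the check is calendar arithmetic. Let d be days from onset to enrolment and D the day of discharge counted from enrolment. Admission and enrolment are taken as the same day (an assumption).

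**1. When the pair ends.** It starts no later than illness Day 10, so it ends at about onset Day 11 at the latest.

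**2. When the Week 4 PCR falls.** On onset day 28 + d; at the earliest on 25 + d or 23 + d with the 3- or 5-day window.

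| d | nominal | 3 days early | 5 days early |
|---|---|---|---|
| 0 | 28 | 25 | 23 |
| 3 | 31 | 28 | 26 |
| 5 | 33 | 30 | 28 |
| 7 | 35 | 32 | 30 |
| 9.1 | 37.1 | 34.1 | 32.1 |

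The nominal visit lies within 28 days of onset only if d = 0, and the earliest permitted visit only if d ≤ 5. The literature review (Table 2) puts onset to admission at 7 to 9.1 days. The enrolment section aims lower ("It is important to enroll the patient as close to the onset of symptoms as possible") but sets no maximum.

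**3. When the merge rule helps.** It applies from D = 28 − 14 = 14, and the swab then falls on onset day D + d. It is inside the window if D + d ≤ 28: for d = 3, D = 14 to 25; for d = 7, D = 14 to 21 (D = 15 gives onset day 22); for d = 10, D = 14 to 18. Section 8 expects most discharges at 5 to 15 days, so the rule reaches the end of that range and longer stays.

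**4. What remains.** With D < 14 and d > 5, no PCR is required between about onset Day 11 and Day 28. At d = 7 the swab-free stretch is 35 − 11 = 24 days.

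**5. How far recovery can move the pair.** A pair taken after enrolment can be brought forward by at most 10 − d days: 3 days at d = 7, 7 days at d = 3.

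**6. How many patients are still positive.** The documents give two answers.

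- Section 2 reports over 90% negative at about 10 days, so under 10% remain positive: fewer than 0.10 × 140 = 14 patients per trial.
- The same section says that "viral shedding may continue well beyond clinical recovery; median duration 20 days (range of 8 to 37 days", and Table 2 gives 20 (17-24) days. Normal approximation: SD = (24 − 17)/1.349 = 5.19. P(> 10) = 1 − Φ((10 − 20)/5.19) = 0.973. P(> 28) = 1 − Φ((28 − 20)/5.19) = 0.062.
- Share clearing between Day 11 and Day 28 on that figure: 0.938 − 0.041 = 0.897 (normal); 0.906 − 0.010 = 0.896 (lognormal with the same median and quartiles).

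These shares refer to Day 10 or 11. Pairs triggered earlier by recovery would find more patients positive. The patients actually affected must also meet the conditions in step 4.

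**7. Would the Week 4 proportion do instead?** At d = 7 the visit is onset day 35. On the Table 2 figure, P(> 35) = 1 − Φ((35 − 20)/5.19) = 0.002, or 70 × 0.002 = 0.1 patient per arm.

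**The case against.** A reader might infer that nobody positive at the first pair can be scored. The documents do not support that.

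- The merge rule can bring the Week 4 PCR to discharge for stays of 14 days or more, and slow recoverers are plausibly the patients still positive. The early-visit window can rescue patients enrolled within 5 days of onset.
- The origin of the 28 days is not stated separately. The bracket follows all-cause mortality, and the primary outcome's 28 days in Section 11.1 attach to a time counted from randomisation. On that origin Week 4 falls on the boundary, not beyond it.
- Such patients can be censored. What is missing is the rule, not the possibility.
- Other swabs may exist. Section 13 lists RT-PCR among the investigations, Section 15 has laboratory work-up daily and at discharge, and the outcome report (Appendix K) has a COVID-19 test field. Section 19.12 leaves detail to procedures not included here.

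A reader might also infer that most clearance is known to fall in the gap. That rests on the Table 2 figure alone, from an inpatient cohort in which Table 3 shows ARDS in 31% and shock in 59%. This trial excludes severe disease, and Section 2 also points the other way.

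These points narrow the concern without removing it. None of the provisions expressly requires a repeat PCR after a positive pair. Fig 1 speaks of skipping Week 4 where Appendix A speaks of merging, and the discharge lists name no PCR. Physician-ordered swabs are optional in an open-label trial and need not be even across arms. Counting from randomisation still leaves no required swab between the pair and Week 4 for patients discharged before Day 14, and a late visit falls outside.

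**Conclusion.** The concern holds in a limited form. For patients positive at the pair, discharged before Day 14 and enrolled more than about 5 days after onset, no required PCR falls between about onset Day 11 and Day 28. Their clearance in that span is not observed, and Section 17.2 gives no rule for them. Among the rest, the recorded time largely follows the day of the pair, so it can differ between arms without a difference in clearance, within the limits of step 5.

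The share affected cannot be settled from the documents: under 10% or about 97% still positive at Day 10, depending on the source. That spread shows conflicting sources, not a large effect. The upper figure assumes a normal shape and a sicker population. The timing result assumes the 28 days run from onset, as the item's own clock suggests.

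This is one timeline within one secondary item of a trial declared exploratory and unpowered. It does not touch the primary outcome, but it merits correction because the remedy is cheap.

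**What to change.** No extra swabs are needed.

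1. In Section 11.2, item 2, state the origin of the window for this outcome and run it from randomisation through the Week 4 visit, including that visit's permitted window.
2. In Section 17.2, analyse time to negative swab as interval-censored between the last positive and the first negative swab, and right-censor patients never negative at their last positive swab.
3. Add a PCR row to the Schedule of Events showing baseline, the swab pair and Weeks 4, 8 and 12.
4. State whether the merge rule applies to the Week 4 PCR, and reconcile the skip wording in Fig 1 with Appendix A, note ii.

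The cost is wording, one table row and one analysis method. The drawback is wide intervals (about 24 days at d = 7), so timing will be imprecise. The proportion negative at Week 4 may be reported descriptively, but it is likely to be near its ceiling and should not replace the outcome.
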